### *Questionnaire development*

The questionnaire of the survey contains established instruments for collecting survey data among key populations, such as LGBTI people, using validated questions and scores. These instruments include questions that have been used throughout the world; thus, their continued use will enable researchers to compare survey results across countries. The standardized instruments provided with these guidelines were designed to be self-administered using electronic or web-based data collection methods.

The questionnaire was built on the following four principles:

1. The process must preserve the complete anonymity of respondents. The privacy and security of respondents must be ensured at every step of the survey;
2. Questionnaire should be as short as possible. Only questions that are necessary should be included;
3. Filling out the online questionnaire should expose participants to no more than minimal risk, such as minimal discomfort, minimal anxiety;
4. Questions selected should have their reliability and validity already demonstrated and their collection should enable triangulation with other surveys.

We followed the following **key steps in questionnaire development**:

- decided on methods for questionnaire administration;
- determined investigation topics (questionnaire domains);
- developed and adapted the questionnaire;
- conducted cognitive testing;
- pre-tested the questionnaire;
- pilot tested the survey tool.

The content of the questionnaire is harmonized with standard indicators and protocol checklists used in behavioural surveillance. The questionnaire is organised as modules focused on topics, such as:

- demographics
- time preference, risk aversion
- socioeconomic status, including a question on financing hormones for transgender people
- behaviours increasing vulnerability to HIV infection (e.g. unprotected receptive anal intercourse, buying sex, selling sex, sharing nonsterile injecting equipment, alcohol and drug use)
- stigma and discrimination in the community, at workplace and health facility (sexual orientation, gender identity, HIV)
- internalized homophobia
- violence
- general health status
- mental health, including depression
- social support network, including family
- HIV prevalence, access to HIV and other health services, HIV services uptake:
  - knowledge of serostatus
  - eligible but not on HIV treatment
  - viral load suppression
  - unsuppressed viral load
  - currently in care

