  - currently on antiretroviral therapy

- discussed pre-exposure prophylaxis
- use of pre-exposure prophylaxis
- health-care stigma

The consensus questionnaire (see [appendix 1](#)) consists of three modules:

- 1st module for LGBTI people, comprising 45 questions;
- 2nd module for MSM and transgender people, comprising 15 questions;
- 3rd module on HIV stigma, comprising 22 questions.

It was our preference to start and finish the survey with relatively comforting questions and statements to reduce any unforeseen discomfort in the participants.

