### Module 3: HIV-related stigma and discrimination

If you are HIV-positive, you may face stigma. Let's talk about it

Choose how you feel about each statement. We understand some questions might sound disturbing. Please share your experience. It will help to create a more inclusive environment for everyone

An exit button is always available at the beginning of each module. Respondent can always scroll back to it

☐ OK (click is required)

62. I am not as comfortable as I used to be in dating since I learned I have HIV

- ☐ strongly agree
- ☐ agree
- ☐ disagree
- ☐ strongly disagree
- ☐ I don't know

63. I disclosed my HIV status on my online profile in the main app I'm using

- ☐ yes
- ☐ no

64. If no, is there any reason you don't mention your HIV status? (tick as many as apply)

- ☐ I revealed it before and couldn't meet anybody
- ☐ I'm afraid of rejection
- ☐ I say I am looking for safe sex (like with a condom) and I do not need to tell them my HIV+ status
- ☐ I don't need to mention it
- ☐ I'm undetectable
- ☐ I don't want to mention it
- ☐ other
- ☐ does not apply to me (I disclosed my HIV+ status on my profile)

65. I changed the way I have sex since I know I'm HIV positive

- ☐ yes
- ☐ no
- ☐ I don't know
- ☐ does not apply

66. Since I've known that I'm HIV-positive, I have sex with:

- ☐ people regardless of their HIV status
- ☐ only HIV-positive partners
- ☐ I don't have sex anymore
- ☐ does not apply

67. Some people avoid touching me once they know I have HIV

- ☐ strongly agree
- ☐ agree
- ☐ disagree
- ☐ strongly disagree
- ☐ I don't know

68. People I care about stopped contacting me after learning I have HIV

- ☐ strongly agree
- ☐ agree
- ☐ disagree
- ☐ strongly disagree
- ☐ I don't know

69. I have lost friends by telling them I have HIV

- ☐ strongly agree
- ☐ agree
- ☐ disagree
- ☐ strongly disagree
- ☐ I don't know

70. Telling someone I have HIV is risky

- ☐ strongly agree
- ☐ agree
- ☐ disagree
- ☐ strongly disagree
- ☐ I don't know

71. I work hard to keep my HIV a secret

- ☐ strongly agree
- ☐ agree
- ☐ disagree
- ☐ strongly disagree
- ☐ I don't know

72. I am very careful whom I tell that I have HIV

- ☐ strongly agree
- ☐ agree
- ☐ disagree
- ☐ strongly disagree
- ☐ I don't know

73. People with HIV are treated like outcasts

- ☐ strongly agree
- ☐ agree
- ☐ disagree
- ☐ strongly disagree
- ☐ I don't know

74. Most people believe a person who has HIV is dirty

- ☐ strongly agree

- ☐ agree
- ☐ disagree
- ☐ strongly disagree

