- ☐ I don't know

75. Most people are uncomfortable around someone with HIV

- ☐ strongly agree
- ☐ agree
- ☐ disagree
- ☐ strongly disagree
- ☐ I don't know

76. I feel guilty because I have HIV

- ☐ strongly agree
- ☐ agree
- ☐ disagree
- ☐ strongly disagree
- ☐ I don't know

77. People's attitudes about HIV make me feel worse about myself

- ☐ strongly agree
- ☐ agree
- ☐ disagree
- ☐ strongly disagree
- ☐ I don't know

78. I feel I'm not as good a person as others because I have HIV

- ☐ strongly agree
- ☐ agree
- ☐ disagree
- ☐ strongly disagree
- ☐ I don't know

79. In the last 12 months, have you ever been excluded from social gatherings or activities (e.g., weddings, funerals, parties, clubs) because of your HIV status?

- ☐ yes, once
- ☐ yes, several times
- ☐ no
- ☐ I don't know
- ☐ it doesn't apply to me

80. Are you currently taking HIV (antiretroviral) treatment? (choose one)

- ☐ yes
- ☐ no, medication is not available at the clinic or pharmacy
- ☐ no, medication is not affordable for me
- ☐ no, I am unable to collect medications at the clinic or pharmacy
- ☐ no, I cannot tolerate medication side effects or am worried about taking the pills
- ☐ no, I do not feel treatment is needed
- ☐ no, I am worried someone would find out my HIV status
- ☐ no, I am not ready to deal with my HIV infection
- ☐ no, I am worried the healthcare workers would treat me badly or disclose my HIV status without my consent
- ☐ no, I do not qualify for treatment in my country because my CD4s are too high
- ☐ no, for other reasons

81. In the last 12 months, have you been told you have an undetectable viral load or are virally suppressed (“good viral load”)?

- ☐ yes
- ☐ no, I have not had a viral load test in the last 12 months
- ☐ no, I had a viral load test and am waiting for the results
- ☐ no, the virus was detectable/I am not virally suppressed
- ☐ I don't know what viral load or viral suppression are
- ☐ I don't have treatment

82. Living with HIV can open new horizons and positively affects us deep inside. Which of the following have been positively affected by your HIV status (tick as many as apply)

- ☐ My self confidence
- ☐ My self-respect
- ☐ My ability to respect others
- ☐ My ability to cope with stress
- ☐ My ability to better take care of my health
- ☐ My ability to contribute to my community
- ☐ Other
- ☐ None of the above

- ☐ PREV (*clicking here brings the respondent to earlier module in case she/he would like to change*)

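### Q82 tells HIV-positive respondents that HIV has positive effects, then asks only about those, so its benefit shares probably run high and cannot be read as a net effect

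*Protocol*

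**What the plan says.** Q82 closes Module 3, which is offered only to respondents who report being HIV-positive. It has three parts:

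- a lead-in: "Living with HIV can open new horizons and positively affects us deep inside";
- the question: "Which of the following have been positively affected by your HIV status (tick as many as apply";
- eight tick boxes: six domains (self-confidence, self-respect, respect for others, coping with stress, care of own health, contribution to the community), an 'other' box, and "None of the above".

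Two statements under Questionnaire development bear on this. One gives the reason for the tone: "It was our preference to start and finish the survey with relatively comforting questions and statements". The other sets a standard for items: "Questions selected should have their reliability and validity already demonstrated".

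The rest of Module 3 deals largely with stigma and its effects. Two examples are Q77, "People's attitudes about HIV make me feel worse about myself", and Q78, "I feel I'm not as good a person as others because I have HIV". Both use an agree/disagree scale.

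**The concern.** The item has two separate weaknesses.

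First, it is leading. The respondent is told that HIV has a positive effect and is then asked for examples. Some who would otherwise have ticked nothing may tick something.

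Second, it runs in one direction. Each domain is either ticked as improved or left blank. A respondent whose coping became worse and one whose coping did not change give the same answer, and no later analysis can separate them.

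What is at stake is how the results are read. A statement that some percentage of HIV-positive respondents gained self-confidence would rest on a prompted answer and would have no matching percentage for loss. The protocol plans country dashboards and advocacy material, and regards this round as a possible baseline for later ones, so the wording could carry forward. It also lists 17 languages including English and concedes, under Limitations, that exact correspondence between languages is almost impossible. An idiomatic prompt may push answers by different amounts in different languages.

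**Working it through.** The protocol gives no expected share for Q82 and no size for a wording effect, so there is no figure to reproduce. The check is mainly textual.

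**Step 1: is the lead-in hedged?** Only in part. In "Living with HIV can open new horizons and positively affects us deep inside" the word 'can' governs the first verb. The second verb stands in the plain indicative, so the positive effect is asserted.

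**Step 2: what can a respondent record in Q82?**
- Improved in a domain: tick it.
- No benefit anywhere: tick "None of the above".
- Worse in a domain: no code.
- Unchanged in a domain: no code.

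Denying all benefit is therefore possible. Separating worse from unchanged is not, either for someone who denies all benefit or for the unticked domains of someone who ticks one.

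**Step 3: is the missing direction recorded elsewhere in Module 3?**
- Loss of ease in dating since diagnosis: Q62.
- Avoidance, lost contacts, lost friends: Q67-69.
- Risk of disclosure and secrecy: Q70-72.
- Guilt and lowered self-worth: Q76-78.
- Exclusion from social events: Q79.

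Q62 and Q77 are worded as negative change, and Q77 and Q78 lie close to Q82's self-confidence and self-respect domains. No Module 3 item records a worsening, because of HIV, in coping with stress, care of own health or contribution to the community.

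**Step 4: why the tick share does not give a net effect.** Let p be the true share improved in a domain and w the share worsened. The net effect is p - w. Q82 shows at best p, and w can lie anywhere from 0 to 1 - p. The net effect is therefore bounded only by

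- lower limit: p - (1 - p) = 2p - 1;
- upper limit: p.

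With an assumed p = 0.25, the limits are 2 × 0.25 - 1 = -0.50 and +0.25. If 35% worsened and 40% were unchanged, the net effect would be 25 - 35 = -10 points, yet Q82 would still show 25%. These inputs are assumptions that show the ambiguity, not estimates.

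**Step 5: the form of the upward bias.** Let s be the true share with any benefit and m the fraction of the others whom the lead-in moves to tick a box. The observed share is s + m(1 - s). With an assumed s = 0.50:

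- m = 0.05: 0.50 + 0.05 × 0.50 = 0.525;
- m = 0.20: 0.50 + 0.20 × 0.50 = 0.60.

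On these assumptions the excess is 2.5 to 10 percentage points. Neither s nor m can be taken from the protocol. Only the direction is argued here.

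**The case against.** The strongest defence is that Q82 is deliberately supportive. It is the last question of a distressing module, and the protocol says it wants a comforting finish. No objective, listed topic or research question uses a positive-impact share or a net effect. The two research questions concern homophobic climate and perceived inequalities, and multiple-choice questions are to be handled case by case. Benefit reported versus not reported is also a usable binary that can be set against the stigma items.

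Most of this stands, and it limits the consequence to Q82's own results. It does not justify the lead-in: a comforting finish does not require a prompt inside a measured item, and the binary is the very quantity that the prompt disturbs.

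A reader might infer more than the protocol supports:

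- **That harm from HIV cannot be recorded.** This is true only inside Q82. Several other Module 3 items record harm, two of them as negative change.
- **That respondents are forced to report a benefit.** They are not, because "None of the above" is offered.
- **That the shares are shown to be inflated by a known amount.** Upward is the plausible direction, but nothing in the protocol measures it.
- **That Q82 breaches the rule "Questions selected should have their reliability and validity already demonstrated".** No source is named for Q82, but the questionnaire does not show sources item by item, so prior validation cannot be judged.
- **That the module introduction, "If you are HIV-positive, you may face stigma. Let's talk about it", has the opposite fault.** It is hedged and tells respondents what follows, beside an exit button. Objecting to it is a matter of preference.

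**Conclusion.** The point holds as a wording defect in one item. Q82 is leading and one-directional. Its benefit shares are likely biased upward by an unknown amount, and they cannot be read as a net effect because worse and unchanged look the same. Other Module 3 items cover harm to self-worth and social life, but leave a gap for coping with stress, care of own health and contribution to the community.

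The direction of bias rests on the ordinary assumption that a suggestive statement placed immediately before a question moves some answers towards it. The ambiguity of an unticked domain needs no assumption, since it follows from the answer format. The stated research questions are not affected.

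**What to change.** 1. Delete the first sentence of Q82. Keep the existing question with *if any* inserted after its first four words, and keep the tick list, 'other' and "None of the above".
2. If a supportive sentence is wanted, show it in a closing line specific to Module 3, after Q82 has been answered. The general thank-you message is not the place, because respondents without HIV see it too.
3. Report Q82 only as benefits reported, never as the net impact of HIV. If the survey has already been fielded, this still applies, with a note that the question followed a positive prompt.
4. If the net effect is of interest, a better / no change / worse answer for each domain would supply it. This is optional: it lengthens the questionnaire and ends it by asking what got worse, against the protocol's preferences for brevity and a comforting finish.

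Steps 1 and 3 cost a small edit to one item in each of the 17 language versions, with the back-translation check, and a slightly less comforting final question. Step 2 adds one further line to translate.

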## Appendix 3: Timeline

[figure not shown]

[figure not shown]

